## 12. Adverse events, Protocol Violations and Procedural Variations

A policies and procedures manual for the project will specify immediate data monitoring and response for anticipated health or mental health issues. Timely data analysis will ascertain if addressable prevalent conditions occur. Data on adverse events and psychological distress will be systematically collected during the trial and reported to the PIs and the Columbia University IRB in order to secure appropriate management of the adverse events as well as to have full documentation of the events for all conditions. The following steps detailed below will be used. All research staff will have completed the Columbia University Office of Projects and Grants' Human Subjects training course, which has received approval from DHHS Office of Human Research Protections to supersede the NIH training course on Protection of Human Research Subjects. The Columbia University training also includes compliance with the Health Insurance Portability and Accountability Act of 1996 (HIPAA). As part of SIG's standard operating protocols, all SIG field, quality assurance, and management staff must complete an intensive,

day-long, structured training program on detecting, addressing, and reporting adverse events before they are allowed to participate in any research. This training which will be conducted by the PIs will also cover how to handle challenging situations, including how to respond to distressed participants and participants who are experiencing life threatening IPV. Also, each research study at SIG conducts an annual 3-hour meeting, first reviewing human subjects protection principles and study-specific procedures, followed by discussion of adverse events for the study over the past year, and role-play exercises which provide a booster to enable staff to handle future adverse events knowledgeably, appropriately, and expeditiously.

Serious adverse events include death, a life-threatening event, an event resulting in hospitalization, prolongation of hospitalization, disability, and incarceration. Serious adverse events, regardless of whether or not they are study related, will be reported to the Columbia University IRB. Other adverse events include breaches of confidentiality (both intentional - e.g., mandated reporting of suicidal/homicidal participants - and unintentional), and non-life threatening psychological distress. The PIs will closely monitor adverse events. The investigative team is aware that the study sample is likely to experience a relatively high incidence of adverse events due to their past/current history of law-breaking behavior, rates of recidivism/re-incarceration reported in the literature, and the high levels of service needs noted earlier in this application. Drawing upon past and ongoing SIG studies, the investigative team designed two forms, (1) Adverse Event: Initial Report and (2) Adverse Event: Full Report, to document adverse events, staff responses, and disposition. The procedures used to track, report, and examine adverse events are described below.

Protocol to Handle Each Adverse Event: Study staff and Fortune providers will identify, manage and document all adverse events. These events may be identified by RAs, the Project Director, PI, or other project staff, including quality assurance staff reviewing audio recordings of interviews, or they may be reported by participants. The following steps will be used to monitor, track, and document procedures used to address each adverse event and subsequent disposition. Within 12 hours of an adverse event being reported/detected, an Adverse Event: Initial Report study report form will be completed by the study staff member or Fortune provider who identified the event. The report form will include date, description of the event, duration, severity, measures taken to ameliorate the adverse event, and disposition-related information (e.g., time spent providing referrals and type of referral (domestic violence shelter, mental health or substance abuse treatment, etc.). The report form will be reviewed and signed by the immediate supervisor who will be responsible for ensuring that appropriate actions have been taken. Within 24 hours of the adverse event, the research staff member or provider who identified the adverse event will discuss the event and response with the Project Director (or the PIs if the Project Director is unavailable) in order to ensure adherence to the protocol for handling the event. (3) Within 48 hours of the adverse event, the investigative team, the Project Director, and any involved staff will ascertain whether the event was related to participation in the study.

An Adverse Event Full Report form will be completed by Drs. [name] and [name]. This full report will contain an attached copy of the initial adverse event form, a summary of information obtained from other documentation and sources that clarify the nature of the event and outcomes, and the determination of whether the event was study related and by what criteria such determination was made. (4) Drs. [name] and [name] will be responsible for reviewing the event occurrence with the appropriate staff to ensure that an adequate response is provided to the

participant. Any serious adverse event whether or not related to the study will be reported to the Columbia University, and the NIDA project officer for the study. The initial adverse event report will be submitted to Columbia University's IRB. This will be followed by submission of the full report to the IRB. In the event that a participant withdraws from the study or the investigator decides to discontinue a participant due to an adverse event, the participant will be monitored by the investigators via ongoing status assessment until (a) a resolution is reached, (i.e. a problem requiring hospitalization is stabilized with no further change expected, or (b) the event is determined to be unrelated to the study.

**Oversight and Review of Adverse Events:** Every two months, the entire investigative team will review all adverse event data to date to determine if systematic trends exist among adverse event data to warrant changes to study protocols and procedures. Any proposed changes will be reviewed with staff at the study sites, and, if needed, external consultant (e. g., other senior investigators conducting federally-funded research on drug abuse and/or criminal justice). The investigative team will also conduct systematic analyses of adverse event data (e.g., associations among frequency, type, severity of adverse events; participant characteristics; and operational aspects of research such as time point, gender of interviewer) to inform future studies with participants in probation, parole or ATI programs as well as recognizing such activities represent a potentially under- researched area of inquiry and scientific endeavor unto itself.

**Protocol Violations and Procedural Variations** – protocol violations and procedural variations from established study protocols and procedures will also be documented by the Project Director and the PI and reported to the IRB using the Protocol Violation and Procedural Variation Forms. A binder of procedural variations will also be maintained by the Project Director.

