### 3. Study Procedures

#### 3.1. The Study Team

This research will be undertaken by the Social Intervention Group (SIG) at the Columbia University School of Social Work. SIG is a multidisciplinary research center with a strong infrastructure and experienced researchers and staff. This study benefits from SIG's extensive

clinical trials experience, an investigative team with longstanding collaborative relationships, and the availability of established and tested protocols from previous randomized controlled trials conducted in community correction sites. The investigative team successfully completed an efficacy trial of Multimedia E-WORTH intervention with drug-involved women under community supervision with the New York City Department of Probation. The investigative team will replicate many of the approaches, procedures, and protocols that achieved success during the pilot trial, which also did not have any adverse events. The study research team will include a project director, a data manager, a clinical supervisor who is a graduate research assistant and 2 research assistants who will be responsible for recruitment, administering assessments and retention of participants. For this study, we will have a service agreement contract with Fortune Society who will hire 6 providers (or 1 full-time equivalent) to conduct the interventions for both study arms. They will not be involved in obtaining informed consent or collecting any data for the study from participants. Fortune Society has multiple longstanding service contracts with the New York City Department of Probation. We will recruit participants from probation, parole or designated ATI program sites located throughout in New York City. We have successfully collaborated with the New York City Department on three randomized controlled trials since 2009. Potential participants in ATI programs or parole will NOT include individuals who are detained in a residential facility or treatment center as a form of sentencing or alternative to incarceration.

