### 3.2. Overview of Study Participation

This randomized controlled trial will be conducted with 420 drug-involved Black women from probation, parole or designated ATI program sites located throughout communities in NYC heavily affected by HIV and STIs. Eligible women will be randomly assigned to: (1) E-WORTH consisting of an individual evidence-based Streamlined HIV Testing session followed by a 4-session group-based multimedia HIV intervention (E-WORTH) or (2) an individual Streamlined HIV Testing session alone (Streamlined HIV Testing), which will serve as the comparison condition. Both conditions will be delivered at two Fortune Society Sites (located in Harlem and in Long Island City). If participants live too far to attend sessions at these sites, Fortune staff may also deliver intervention sessions at our community research site or at a NYC DOP site approved by the appropriate DOP Assistant Commissioner. Repeated assessments will occur at baseline and 3, 6, and 12-months post intervention. For participants residing out of New York City during their follow up period, or are otherwise prevented from traveling to study sites to complete a follow up assessment, we will send a link to follow up assessments directly to the participant's e-mail on a password protected PDF document. We will conduct repeated assessments and qualitative in-depth interviews on multi-level factors that may influence the effectiveness of E-WORTH and Streamlined HIV Testing on study outcomes with Fortune providers delivering the interventions, frontline probation, parole or designated ATI program staff (e.g. probation officers), probation administrators and probation clients. Self-reported data on behavioral outcomes will be collected from participants via audio computer-assisted self-interview (ACASI). Primary outcomes will be measured via biological assay for infection by *Neisseria gonorrhea*, *trichomonas*, and *Chlamydia trachomatis*, the most common STIs found among women in NYC.

We will also conduct qualitative interviews with 20 E-WORTH participants who reported episodes of homelessness and depression when completing assessments at baseline, 3-, 6- and/or 12-month. The goal of these interviews is to better understand the relationship between

homelessness and depression among women involved in the criminal justice system who are also at risk for HIV and other STIs.

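### Adverse events are found through contact, contact is unequal by arm and no common query is described, so control-arm events may be under-detected relative to E-WORTH

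*Supplement*

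**What the plan says.** Section 12 opens with a general undertaking: "Data on adverse events and psychological distress will be systematically collected during the trial", with full documentation for all conditions. The steps that follow concern reporting after detection (an initial form within 12 hours, discussion within 24, a relatedness judgement within 48). On detection itself the text says "Study staff and Fortune providers will identify, manage and document all adverse events". It then adds "These events may be identified by RAs, the Project Director, PI, or other project staff, including quality assurance staff reviewing audio recordings of interviews", and closes the list with "or they may be reported by participants". It names no question, instrument or visit at which adverse events are actively sought.

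The arms differ in provider contact (Section 3.2). One is "E-WORTH consisting of an individual evidence-based Streamlined HIV Testing session followed by a 4-session group-based multimedia HIV intervention"; the other is "an individual Streamlined HIV Testing session alone (Streamlined HIV Testing), which will serve as the comparison condition". Under Section 3.6 each E-WORTH group session lasts 1.5 hours and covers partner violence, drug use, criminal justice involvement and service needs. The control session is two five-minute explanations around a 20-minute wait. Section 3.9 has all sessions in both conditions recorded and 10% reviewed.

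On use of the data, Section 12 has the team look for trends every two months that might warrant protocol changes, and adds: "The investigative team will also conduct systematic analyses of adverse event data". Section 13 has the DSMB review adverse events.

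Section 3.1 says of the Fortune providers: "They will not be involved in obtaining informed consent or collecting any data for the study from participants".

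**The concern.** If events come to light when a participant talks to someone, the arm with more talking will show more of them. E-WORTH sessions invite discussion of the very matters that count as adverse events here, with a provider present who is expected to file the form. The comparable control event has fewer prompted occasions to surface.

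The protocol also gives reasons to expect some real E-WORTH harm. Section 11 warns that safer-sex negotiation may anger partners and that group members may disclose confidences. A true excess is therefore plausible, and contact-dependent detection cannot separate it from closer listening. An apparent excess could prompt an unnecessary protocol change, or a genuine one could be put down to extra contact. Section 12 expects a relatively high incidence of adverse events, so the counts may be large enough to be read this way.

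**Working it through.** The documents give no adverse event rate, detection rate or safety power, so there is no plan figure to reproduce. The check has three parts.

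**1. Detection routes, side by side**

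- *Provider sessions (3.2, 3.6):* 5 in E-WORTH, 1 in control.
- *Session recordings (3.9):* the same 10% sampling, hence 0.10 × 5 = 0.5 sampled sessions per E-WORTH woman against 0.10 × 1 = 0.1 in control. Section 12 itself speaks of recordings of interviews; the link to sessions comes from 3.9.
- *Follow-up visits (3.4):* 3 in each arm. The ACASI covers partner violence, depression, PTSD and justice involvement, but is self-completed in private and stored automatically (3.4, 9). No route from its answers to an adverse event form is stated.
- *Retention contacts (3.8):* biweekly in both arms by phone, text, email or mail, check-in calls included. No event question is specified.
- *Participant report (12):* open to both arms, unprompted.

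**2. Contact counts after randomization**, assuming full attendance. Baseline is left out because it precedes randomization (8.1).

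- Sessions only: 5 / 1 = 5.0.
- Sessions plus three follow-ups: (5 + 3) / (1 + 3) = 8 / 4 = 2.0.
- Adding 26 biweekly contacts (assumed, 52 / 2): 34 / 30 = 1.13.

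**3. Illustrative ratio of detected events when true rates are equal**

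Let d be the chance that one in-person contact surfaces an event, s the chance that a route shared by both arms finds it, and k the number of contacts (8 or 4). Then P(detected) = 1 − (1 − s)(1 − d)^k. Both d and s are assumptions.

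Example with d = 0.10. At s = 0: (1 − 0.9^8) / (1 − 0.9^4) = 0.570 / 0.344 = 1.66. At s = 0.5: 0.785 / 0.672 = 1.17.

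| s | d = 0.05 | d = 0.10 | d = 0.20 | d = 0.40 |
|---|---|---|---|---|
| 0 | 1.81 | 1.66 | 1.41 | 1.13 |
| 0.25 | 1.29 | 1.33 | 1.26 | 1.09 |
| 0.5 | 1.13 | 1.17 | 1.15 | 1.06 |
| 0.75 | 1.05 | 1.07 | 1.07 | 1.03 |
| 0.9 | 1.02 | 1.02 | 1.03 | 1.01 |

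This model lets every event surface at every contact, which is generous to the concern: an event in month 9 cannot be disclosed in a session held months earlier. Suppose instead that the four extra contacts help only for events in a session window of w weeks out of 56 (w = 4 to 8, assumed), with three looks at all other events. The ratio is then [f(1 − (1 − d)^7) + (1 − f)(1 − (1 − d)^3)] / (1 − (1 − d)^3), with f = w / 56. For d = 0.10 to 0.40 it runs from 1.02 to 1.13.

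If somebody tested the arms with 210 women each, a true event rate of 20% (assumed) and d = 0.05 to 0.20, the chance of a spurious two-sided p < 0.05 in the E-WORTH direction would be about 29% to 36% at s = 0, 7% to 10% at s = 0.5 and about 3% at s = 0.9. The nominal figure in that direction is 2.5%.

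**The case against.** A reader might infer that E-WORTH events will certainly be over-counted and that the final safety comparison will be uninterpretable. The documents do not support this, for four reasons.

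- *Shared routes exist.* Participants may report events themselves, and check-in calls and follow-up visits are the same in both arms. Death, hospitalization and incarceration would often emerge through tracking in either arm; incarceration also ends participation (11.1).
- *No by-arm comparison is written.* The two-monthly review does not mention arm, and the example factors for adverse event analysis are participant characteristics, time point and interviewer gender. The efficacy and futility rules in Section 13 rest on outcome results and required sample size.
- *Two important harms are measured equally elsewhere.* Partner violence and recidivism are secondary outcomes (1.2), and the same assessment is used at every visit (5).
- *The detail may sit elsewhere.* Section 12 refers to a policies and procedures manual and two report forms, none of which is shown.

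All four stand and limit the claim. They do not remove it. Participant report is unprompted, no route from the ACASI to the adverse event forms is described, and nothing in the text secures a high rate of shared detection. A safety board in a two-arm trial can be expected to look by arm, and Section 13 gives it a decision on termination for safety.

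The tension between Sections 3.1 and 12 over Fortune providers is minor. Section 3.4 already has them record attendance and adherence, so 3.1 can be read as meaning consent and assessment data. It needs clarifying and is not a serious contradiction.

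**Conclusion.** The point holds as a risk of unequal ascertainment. As described, detection depends on contact, contact differs by design (5 sessions against 1; 8 against 4 in-person contacts after randomization), and no common query is set out. The likely direction is under-detection in control relative to E-WORTH, chiefly for distress, partner violence and confidentiality breaches and less for serious events. The size cannot be determined from the documents: the illustrative ratio spans about 1.0 to 1.8, and its upper end requires that shared routes find nothing. The range rests on assumed values of d and s, full attendance and independent contacts. It matters only where adverse events are read by arm, which the plan neither specifies nor rules out. This is a cheap improvement to the stated method; it does not threaten the primary analysis.

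**What to change.** In Section 12, have the RA ask the same short adverse event query in both arms at the existing 3-, 6- and 12-month visits (hospitalization, arrest or jail, partner violence, distress and breach of confidentiality since the last visit), on the visit checklist already described in Section 3.3. Where a follow-up is completed remotely (3.2), the RA can ask it by phone.

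Add a source-of-detection field to the Initial Report form. Base the main by-arm summary on query-detected events plus deaths, with the number of women queried in each arm. Show all events beside it, by arm and source. Session-detected events must not be left out: breaches of confidence and distress arising in group sessions can occur only in E-WORTH, so dropping them would hide genuine intervention harms. The full table is also needed for women who are never queried, for example those whose participation ended on incarceration (11.1).

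Clarify in Section 3.1 that Fortune providers do complete adverse event forms.

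With an identical query at identical times, and similar attendance and candour in both arms, equal true rates give an expected ratio of 1.0 for query-detected events. The cost is protocol wording, one form field, a few minutes per visit and one extra table. Reporting to the IRB and NIDA is unchanged.

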### 3.5. Randomization

Consistent with an intention-to-treat approach for data analyses, participants will only be considered enrolled in the trial when they have been randomly assigned to a study arm. We will implement urn randomization to “force” a balance (without adding bias) between study arms with respect to the number of women per arm so that half of the women will be randomized to E-WORTH and immediately receive the individual Streamlined HIV test session followed by 4 E-WORTH group sessions and half will be randomized to and immediately receive the Streamlined HIV Testing session alone. The randomization program, which has been adapted from our previous RCTs, will also feature a combination of randomization and assignments to balance the number of women per condition per site so that the number of women assigned to each condition will be distributed across probation, parole or designated ATI program and study sites. In addition, participants randomized to the intervention arm will complete the intervention individually if less than 4 participants are enrolled at a given site in 28 calendar days. Additionally, the assignment window during the Treatment as Usual condition assignment phase will open after the first participant is assigned. We will explain the randomization process to participants during informed consent. The randomization and assignment protocol will also

ensure moderators of intervention effects assigned to study arms, thus minimizing the possible introduction of bias that can occur with urn randomization or block permutation techniques.

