Obtaining informed consent will be documented with the use of a written consent form. The consent form provides details of the study procedures, risk, benefits, nature of confidentiality, study contact information, the nature of voluntary participation. The consent process also covers the information on reimbursement for time. Data will be destroyed with no questions asked upon a subject's request. The consent form will state that participants may withdraw from the study without penalty at any time for any reason with no explanation. Participants will also be asked about agreeing for the intervention session to be audio recorded solely for the purposes of quality assurance. The consent form indicates that such agreement is not a requirement to participate in the study and informs the participant that any portion or the entire recording will be erased upon her/his request at any time, including during or any time after the interview. Before a participant signs the informed consent form, staff will thoroughly review the form, ask if the participant understands the content of the consent form, and answer any questions that may arise. As noted above, informed consent will not be considered obtained (and thus, the participant excluded from the study) if a potential participant is unable to state the following after reviewing the consent form: (1) the nature and extent of participation in the study; (2) the risks involved with participation; and (3) the potential benefits of participation in the study. Informed consent for Probation, parole or an ATI program client participants for in-depth interviews: We will follow the general same consent procedures described above for participants who are randomly selected to complete a face-to-face in-depth interview. For randomly selected participants who express interest in completing an in-depth interview. Informed consent for Probation, parole or an ATI program staff and Fortune providers for Aim 4 study activities: For probation, parole or an ATI program staff and providers who express interest in being interviewed in the longitudinal survey, research assistants will similarly go through the informed consent process in a private location and ensure participation is entirely voluntary, stressing that participation is in no way required for employment purposes, and their employer will not know whether or not they chose to participate.

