### 11.1 Vulnerable Populations

The proposed study will not involve participants who meet the criteria for classification as prisoners. As the study will involve participants who are in probation, parole or ATI programs, there is a likelihood that some participants may become incarcerated. If a participant becomes incarcerated or detained, the adverse events protocol described below will be followed, and the participant's involvement in the study will be discontinued.

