## **Data Analyses Plan:**

The analytic approach is built upon the investigative team's prior HIV prevention randomized clinical trials, including an intention-to-treat approach, handling missing data using both complete case and multiple imputation approaches, attrition analyses to investigate non-ignorable nonresponse, and sensitivity analyses to ascertain robustness of findings against violation of model assumptions (e.g., distribution requirements, heteroscedasticity, independence). Mixed-Effects Generalized Linear Models will be used to account for the non-independence in measures due to repeated measures with the same person. These models build upon  $g(E[(Y_{ij}|\mathbf{x}_{ij}]]) = \mathbf{x}'_{ij}\boldsymbol{\beta}$  where  $Y_{ij}$  is the outcome variable of interest for the  $i$ th participant at the  $j$ th timepoint. The components of  $\boldsymbol{\beta}$  will be intervention assignment, baseline attributes for the outcome variable, and selected sociodemographic variables based on the unbalanced randomization or relevant literature. The  $g(a)$  function represents a link function that can properly model the outcome variable as a function of measurement unit or distribution. Hypothesis testing follows the form "Assignment to E-WORTH will be associated with significantly lower/higher on outcome variable  $Y$  at the 12-month follow-up or over the follow-up period compared to assignment to the control condition where 'lower' or 'higher' is chosen in the direction of reduced risk. To test the difference in the new incidence of any STI (primary outcome) at the 12-month follow up, logistic regression models will be used. To test the effects for behavioral outcomes over the entire follow-up period, mixed-effects Poisson or negative binomial regression will be used for the number of condomless acts of sex (primary outcome), mixed-effects linear regression will be used for proportion of protected acts of intercourse, and mixed-effects logistic regression models will be used for binary behavioral outcomes.

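### Discontinuation for incarceration or another adverse event has no provision for collecting outcomes afterwards, so 12-month data may be lost avoidably and unequally by arm

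*Supplement*

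**What the plan says.** Section 11.1 (Vulnerable Populations) deals with a participant who becomes incarcerated or detained. The adverse-event procedure is followed and "the participant's involvement in the study will be discontinued". Section 12 counts incarceration as serious: "Serious adverse events include death, a life-threatening event, an event resulting in hospitalization, prolongation of hospitalization, disability, and incarceration". It also expects that "the study sample is likely to experience a relatively high incidence of adverse events".

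Section 12 then makes the same provision for a woman who withdraws from the study and for one who is discontinued because of any adverse event: when "the investigator decides to discontinue a participant due to an adverse event, the participant will be monitored by the investigators via ongoing status assessment". That is safety follow-up, and it lasts until the event resolves or is judged unrelated to the study. Outcome visits are not mentioned. Section 8 (Informed Consent Process) states that "participants may withdraw from the study without penalty at any time for any reason with no explanation".

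On the analysis side, section 3.5 (Randomization) says: "Consistent with an intention-to-treat approach for data analyses, participants will only be considered enrolled in the trial when they have been randomly assigned". The Data Analyses Plan promises a similar approach, "including an intention-to-treat approach, handling missing data using both complete case and multiple imputation approaches", together with attrition analyses. The primary STI outcome is tested at 12 months. In section 3.7 (Compensation) the 3- and 6-month payments are for interviews, and only the 12-month payment includes an STI test. An unscheduled retesting payment is also listed. Section 1.2 makes recidivism a secondary outcome.

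**The concern.** An intention-to-treat comparison needs outcomes from the women who were randomized, including those who stop the intervention. Here an event after allocation can end a woman's involvement, and the plan does not say that her assessments go on.

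The loss may not be the same in both arms, and it could run either way:

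- **More loss in E-WORTH.** That arm adds four group sessions. Section 11 names disclosure by other group members and partner anger over safer-sex negotiation as risks. Section 12 lets providers and reviewers of recordings identify events, so more contact means more chances of detection.
- **More loss in control.** If E-WORTH reduces recidivism, as the secondary aim hopes, more control women would be incarcerated and discontinued under section 11.1.

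Section 12 gives no criteria for the investigator's decision, and section 13 states that the principal investigators and co-investigators are unblinded. With no scheduled swab between baseline and 12 months, imputation of the STI outcome must rest mainly on the baseline swab and self-report.

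**Working it through.** **Inputs from the documents.** Section 2.3 gives control cumulative incidence 20.5%, a 50% reduction (so 10.25%), effective sample 372, then 378 after clustering, then 420 after a 10% loss. Section 3.5 gives 1:1 allocation. The stopping rules in section 13 give a two-sided 5% level; the power paragraph states none for the primary outcome. The documents give no discontinuation rate and no STI risk among discontinued women, so both are assumed below.

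**Step 1: the plan's own figures.** 378 / (1 − 0.10) = 420, exactly. With 372 / 2 = 186 per arm, a two-proportion test of 20.5% against 10.25% has 78.5% power, close to the stated 80%. A Poisson-regression formula gives a total of 364 against 372, within 3%. The implied design effect is 378 / 372 = 1.016.

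**Step 2: the passages side by side.**

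| Place | Effect on outcome collection |
|---|---|
| 11.1, incarceration or detention | Involvement ends; stated outright |
| 12, any adverse event, investigator's decision | Safety monitoring described; outcome visits neither stopped nor continued |
| 8 and 12, woman withdraws | From the study as a whole; no intermediate level offered |
| 3.5 and Data Analyses Plan | All randomized women belong to the comparison |

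For incarceration the loss is explicit. For other adverse events it is an inference, drawn from the silence of section 12, from its pairing of withdrawal from the study with discontinuation, and from the way section 11.1 uses the word.

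**Step 3: complete-case bias when there is no true effect.** Let p = 0.205 in both arms, d the fraction lost and s the STI risk among those lost. The observed risk is (p − d·s) / (1 − d).

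- E-WORTH, d = 8%, s = 40%: (0.205 − 0.032) / 0.92 = 18.8%.
- Control, d = 2%, s = 40%: (0.205 − 0.008) / 0.98 = 20.1%.
- Spurious difference: 1.3 points, or 1.3 / 10.25 = 13% of the planned effect.
- With about 185 per arm, SE = √(2 × 0.205 × 0.795 / 185) = 0.042. The shift is 0.013 / 0.042 = 0.31 SE, so two-sided rejection is about 6% instead of 5%.
- Equal loss at equal risk, 8% in both arms: 18.8% against 18.8%, no bias.

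**Step 4: complete-case bias when the planned effect is true.** Let discontinued women have twice the risk of retained women. The retained risk is p / (1 − d + 2d).

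| Loss, control / E-WORTH | Control | E-WORTH | Risk ratio (true 0.50) |
|---|---|---|---|
| 10% / 10% | 18.6% | 9.3% | 0.50 |
| 10% / 15% | 18.6% | 8.9% | 0.478 |
| 10% / 5% | 18.6% | 9.8% | 0.524 |
| 20% / 10% | 17.1% | 9.3% | 0.545 |

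Bias in the risk ratio needs loss that differs by arm, or a different relation between loss and risk in each arm. Its direction follows the direction of the imbalance.

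**Step 5: power.** With N = 420 and design effect 1.016, the two-proportion test has 78.5% power at the planned 10% loss, 76.1% at 15% and 73.6% at 20%.

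**The case against.** A reader might infer that every woman discontinued for an adverse event is followed for that event and nothing else, that her swab and self-report are lost, and that intention-to-treat is thereby broken. The documents do not support that much. The word 'only' is not in section 12, which sets a safety duty and neither cancels nor continues outcome visits. Randomized women stay in the analysis set, imputation, attrition and sensitivity analyses are planned, and a 10% loss is built into the sample size. Data lost after a woman chooses to leave are her right to withhold and no fault of the plan.

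Other provisions also soften the picture. Section 11 lets a distressed woman end one interview or session without leaving the study. The retention procedures in section 3.8 are not tied to session attendance. Section 3.2 allows self-report by an e-mailed link.

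The assumed rates come from no passage. Section 3.1 reports no adverse events in the pilot, and the earlier WORTH trial lost about 9% from all causes at 12 months. Section 12 attributes the expected events to history and service needs, not to sessions. More extreme inputs give more: 12% against 2% with 50% STI yields 16.5% against 19.9%, 3.4 points, and a false-positive rate of about 13%. But a 12% loss from adverse events alone exceeds that earlier all-cause figure, so I do not rely on it.

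All of this stands, and it limits the point. It does not remove it. No provision says what happens to outcome collection once a woman is discontinued, section 11.1 ends involvement outright, and the 10% allowance protects sample size, not against unequal loss.

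**Conclusion.** The point holds in a limited form. The plan ends involvement on incarceration, allows discontinuation for any adverse event, and has no rule that keeps outcome collection going afterwards. This puts the intention-to-treat comparison at risk from avoidable missing data; it does not break it. Loss of outcomes is explicit for incarceration and inferred for other events.

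The size cannot be known from the documents. Under the assumed 8% against 2% loss with 40% STI among those lost, the complete-case shift is about 1.3 points and the false-positive rate about 6%, which is modest. It is zero with equal loss at equal risk, and could favour either arm. These figures describe complete-case analysis; imputation could reduce the bias, but with little follow-up STI information to draw on. The point is worth making because the remedy is cheap, not because a large bias has been shown.

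**What to change.** - In sections 11.1 and 12 and in the consent text, state that discontinuation by the investigator for an adverse event does not by itself end outcome collection. The scheduled 3-, 6- and 12-month self-interviews and the 12-month swab stay on offer unless the woman withdraws consent for assessments.
- For incarcerated or detained women, reconcile section 11.1 with the intention-to-treat plan, for example by allowing assessment after release within the study's ethics approval.
- Offer women who wish to withdraw the choice of leaving sessions while keeping assessments. Full withdrawal remains open to them at any time.
- Record the level of discontinuation and its reason, and report both by arm.

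When sessions or an individual assessment are stopped for safety is left as it is. The cost is a protocol paragraph, an edit to the consent and withdrawal forms, and some extra tracking. The visits are already scheduled and a remote route for self-report exists; the swab still has to be collected at a study location.
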